## Abstract

**Background:**

Culminating evidence shows that current care does not optimally meet the needs of persons with parkinsonism, their carers and healthcare professionals. Recently, a new model of care was developed to address the limitations of usual care: Proactive and Integrated Management and Empowerment in Parkinson’s Disease (PRIME Parkinson). From 2021 onwards, PRIME Parkinson care will replace usual care in a well-defined region in The Netherlands. The utility of PRIME Parkinson care will be evaluated on a single primary endpoint (parkinsonism-related complications), which reflects the health of people with parkinsonism. Furthermore, several secondary endpoints will be measured for four dimensions: health, patient and carer experience, healthcare professional experience, and cost of healthcare. The reference will be usual care, which will be continued in other regions in The Netherlands.

**Methods:**

This is a prospective observational study which will run from January 1, 2020 until December 31, 2023. Before the new model of care will replace the usual care in the PRIME Parkinson care region all baseline assessments will take place. Outcomes will be informed by two data sources. We will use healthcare claims-based data to evaluate the primary endpoint, and costs of healthcare, in all persons with parkinsonism receiving PRIME Parkinson care (estimated number: 2,000) and all persons with parkinsonism receiving usual care in the other parts of The Netherlands (estimated number: 48,000). We will also evaluate secondary endpoints by performing annual questionnaire-based assessments. These assessments will be administered to a subsample across both regions (estimated numbers: 1,200 persons with parkinsonism, 600 carers and 250 healthcare professionals).

**Discussion:**

This prospective cohort study will evaluate the utility of a novel integrated model of care for persons with parkinsonism in The Netherlands. We anticipate that the results of this study will also provide insight for the delivery of care to persons with parkinsonism in other regions and may inform the design of a similar model for other chronic health conditions.

## Background

Parkinsonism, which aside from its most common subtype Parkinson’s Disease (PD) includes various forms of atypical parkinsonism, is a rapidly growing source of disability globally [1, 2]. Current care is not designed optimally to meet the specific needs of persons with parkinsonism [3, 4]. To understand the specific challenges in current care for parkinsonism, several qualitative and quantitative pilot investigations have been conducted over the last few years, revealing specific unmet needs of persons with parkinsonism, their carers and healthcare professionals involved in their care [5–11]. In particular, usual care for persons with parkinsonism is constrained by a lack of multidisciplinary collaboration and poor continuity, delayed detection and reactive management of symptoms, and difficulties in accessing healthcare professionals with appropriate expertise [12]. Furthermore, there is a lack of empowerment and involvement for persons with parkinsonism and carers, care is not managed close to home, and care typically follows a ‘one size fits all’ approach [12]. These limitations not only negatively influence quality of life and associated other measures of health of people with parkinsonism (reflecting the ‘health’ dimension), but also have a negative economic impact (‘cost of healthcare’) as well as burdening persons with parkinsonism and carers (‘patient and carer experience’) and impairing professional fulfilment of healthcare professionals (‘healthcare professional experience’) [9, 13, 14]. In combination, these four dimensions reflect a previously described framework to evaluate the quality of care (‘Quadruple Aim’) [15, 16].

Recently, the recognition of these challenges has been used to develop an integrated care model that focuses on regional collaboration: Proactive and Integrated Management and Empowerment in Parkinson’s Disease (PRIME Parkinson) care [17]. The concept of PRIME Parkinson care aims to address the unmet needs of persons with parkinsonism and carers, while also accommodating preferences of healthcare professionals involved in their care as much as possible and keeping the costs neutral. The components of PRIME Parkinson care are summarized in Table 1. PRIME Parkinson care will be administered to persons with parkinsonism irrespective of whether their underlying disease is PD or atypical parkinsonism, because of the large overlap in problems that persons with these diseases face, and also because there is always a certain degree of diagnostic uncertainty when it comes to the clinical distinction between PD and atypical parkinsonism [18, 19].

**Table 1 Tab1:** Core elements of the PRIME Parkinson care intervention

Usual care	PRIME Parkinson care
Lack of multidisciplinary collaboration and continuity of care	Deliver integrated care and continuity of care
Issues detected late and managed reactively	Manage issues early and proactively
Difficult to access healthcare professionals with appropriate expertise in a timely fashion	Facilitate access to specialised healthcare professionals
Lack of empowerment and involvement for persons with parkinsonism and carers	Educate and empower persons with parkinsonism and carers
Care not managed close to home	Organise care close to home
'One size fits all' treatment and focus mainly on motor symptoms	Deliver personalised care and "precision" medicine

Note that we have previously published a full description of the PRIME Parkinson care intervention [17]

The purpose of this paper is to describe how the research evaluation of PRIME Parkinson care in the Netherlands (PRIME-NL) has been designed. There is a parallel but independent research evaluation in the United Kingdom which will reported elsewhere and follows the same guiding principles but with a different methodology. PRIME-NL will be implemented for persons with parkinsonism in the PRIME Parkinson care region from 2021 onwards, replacing usual care for all persons with parkinsonism in the region; it will not be implemented as a research intervention [12]. We will prospectively evaluate the utility of PRIME Parkinson care, compared to usual care in other regions of The Netherlands. The evaluation will span each dimension of the Quadruple Aim framework: health, patient experience, healthcare professional experience, and cost of healthcare [15, 16]. As the model also targets the quality of care for carers of persons with parkinsonism, we will additionally evaluate the model’s utility on a fifth dimension: carer experience.

## Methods

### Overview of study design and data sources

This is a prospective observational study, which will run from January 1, 2020 through December 31, 2023. The study comprises two data sources: healthcare claims-based data and questionnaire-based data. We will use healthcare claims-based data to compare all persons with parkinsonism in the PRIME Parkinson care region (Index sample) with all persons with parkinsonism across other regions in The Netherlands (Control sample). The choice to include four community hospitals in the PRIME Parkinson care region was determined by the available funding. The choice for these specific hospitals was based on their geographical proximity (i.e., a 25 km radius) to the Radboud University Medical Centre, as well as a prior history of collaboration in clinical and research settings [20, 21].

Furthermore, we will perform annual questionnaire-based assessments in a subsample which will be approximately equally divided over the PRIME Parkinson care and usual care regions (estimated numbers: 1,200 persons with parkinsonism, 600 caregivers and 250 healthcare providers). Since PRIME Parkinson care will be implemented in the Index region from January 1, 2021 onwards, we consider the first year (January 1, 2020 through December 31, 2020) as the baseline observational period and the following three years (January 1, 2021 through December 31, 2023) as the implementation period. An overview of the patient study population is provided in Fig. 1.

**Fig. 1 Fig1:**
[figure not shown]
Overview of study population

We note that both data sources serve complementary purposes: we will use healthcare claims-based data to evaluate the primary endpoint of the health dimension, which is a composite measure of parkinsonism-related complications, as well as other endpoints of health and cost of healthcare. We will use questionnaire-based data to evaluate other endpoints of health, patient and carer experience and healthcare professional experience (Table 2).

**Table 2 Tab2:** Data sources, categorised by dimension

Dimension	Data source(s)
Health^a^ *(contains the primary endpoint: parkinsonism-related complications)*	Healthcare claims & Questionnaires
Cost of health care	Healthcare claims
Patient and carer experience	Questionnaires
Healthcare professional experience	Questionnaires

^a^Of note, this dimension reflects health of people with parkinsonism

#### Healthcare claims-based data

Healthcare claims-based data will be provided by Vektis, which is the Dutch health care information centre and has healthcare expenditure data on all insured individuals in The Netherlands, which embodies > 99.8% of the Dutch population (± 17.2 million people) [22, 23].

#### Questionnaire-based data

Participants will self-administer questionnaires electronically, with the exception of the telephone Montreal Cognitive Assessment (MoCA) which will be conducted over the phone for all participants. Participants who are not able to complete electronic questionnaires will be provided with two alternatives: paper-based self-administration or telephone-based interview administration. We will conduct annual assessments between 2020 and 2023, i.e. one baseline and three follow-up assessments at 12, 24 and 36 months after enrolment.

#### Eligibility criteria and definition of regions

Persons with a clinical diagnosis of parkinsonism, except those in whom the cause is medication use (which is potentially reversible), who receive their treatment in a community hospital will be eligible for the study. In this context we refer to non-university medical centres as a community hospital. The PRIME Parkinson care region consists of four community hospitals: Bernhoven Ziekenhuis, Canisius Wilhelmina Ziekenhuis, Maasziekenhuis Pantein, Rijnstate Ziekenhuis. In Fig. 2 the PRIME Parkinson care region is presented visually. Persons who receive parkinsonism treatment in the PRIME Parkinson care region will be compared to persons in a community hospital outside the above-defined region who receive usual care for parkinsonism. There are 60 community hospitals in the usual care region. In both groups, the targeted population is representative of the broad spectrum of persons with parkinsonism who are treated in a community hospital.

**Fig. 2 Fig2:**
[figure not shown]
Overview of PRIME Parkinson care and usual care regions and study timeline

Detailed inclusion criteria for persons with parkinsonism, carers and healthcare professionals are presented in Table 3. Carers are eligible to participate even if the person with parkinsonism whom they care for does not participate in this study. For those carers, we have added questions on the characteristics of the person with parkinsonism for whom they provide care.

**Table 3 Tab3:** Inclusion criteria

*Research population*	Inclusion criteria
Persons with parkinsonism	Have a clinical diagnosis of parkinsonism, except drug-induced parkinsonism; have visited the Neurology outpatient clinic of a community hospital centre at least once during the last year; willing and able to provide informed consent^a^
*Carers*	Be designated as the primary carer by a patient who is eligible to participate; willing and able to provide informed consent^a^
*Healthcare professionals*^b^	Work as a certified nurse, physical therapist, occupational therapist, speech-language therapist or neurologist; have seen at least 5 persons with parkinsonism in the previous year; willing and able to provide informed consent^a^

^a^For inclusion in questionnaire-based assessments only. Carers are eligible for participation even if the person with parkinsonism who they care for does not participate in this study. For those carers, we have added additional questions on characteristics of the person with parkinsonism for whom they provide care. ^b^While it is not feasible to assess healthcare professionals from each field of expertise involved, we intend to longitudinally assess Healthcare Professional Experience in a sample that reflects that diverse composition, comprising nurses, physical therapists, speech-language therapists, occupational therapists and neurologists

This is a closed cohort study, meaning there will be no further inclusion after the baseline assessment round.

#### Recruitment process in the questionnaire-based study

The recruitment of persons with parkinsonism comprises three phases: actively informing potential participants (phase 1), providing additional information to those who are interested (phase 2), and obtaining informed consent (phase 3).

Phase 1 entails publicising the study through various channels. First, invitation letters will be sent to members of ParkinsonNEXT, a web-based platform for persons with parkinsonism and their carers who have expressed an interest in participating in research. Second, the Parkinson Vereniging (Dutch Parkinson patient association) will send newsletters and share posts on their website. Third, a brochure with a reply card has been designed that will be shared with potential participants at different events organized for persons with parkinsonism or their carers, including -among others- ParkinsonNEXT innovation and research events and the national ParkinsonNet congress. One additional recruitment strategy will be applied in the PRIME Parkinson care region only, to increase the likelihood that the target sample size in that region will be reached: hospital-based neurologists in the PRIME Parkinson care region will send information letters to all persons with parkinsonism affiliated to their hospital.

In phase 2 persons with parkinsonism can indicate their interest to receive more information about the study on the study website (https://www.parkinsonnext.nl/prime/) or by contacting the assessment team via telephone, email or sending a reply card by post. Persons with parkinsonism can only participate if they have provided informed consent. Persons with parkinsonism who express an interest by calling or responding via the website will be provided with more information about the study by a call from a member of the research team. In phase 3, persons with parkinsonism who indicate continued interest in participating in the study during the call will receive an information letter and consent form by e-mail or post. Persons with parkinsonism can then sign the informed consent form. Given the focus of our recruitment strategies, we anticipate that the majority of carers will be informal carers of a person with parkinsonism, however, we cannot rule out that some carers had formal training or are professional carers. The PRIME Parkinson Care model will replace usual care in the designated region. This means that, in theory, all persons with parkinsonism will receive the PRIME Parkinson Care model. However, we consider it unlikely that uptake of each component of the model will be complete. There has been preliminary work and ongoing comparable studies which suggest how the uptake/recruitment of the evaluation of the new model of care itself might work out. In pilot investigations of individual components of the model the dropout rate was 5% after 8 months [20]. Based on preliminary work and comparable ongoing studies, we expect that it is achievable to generate the necessary participation and to be able to obtain commitment from participants for the duration of the study [20, 21].

The recruitment process for carers will be almost identical to the recruitment process for persons with parkinsonism, with one exception: we will also inform carers about the study through participating persons with parkinsonism. After informed consent has been provided, persons with parkinsonism are contacted by telephone and asked if they have a carer and whether this person is potentially also interested in participating in this study.

Healthcare professionals will be asked to participate through an invitation mail that is sent out via ParkinsonNet, a community-based professional network of healthcare providers treating persons with parkinsonism [24, 25]. Also, healthcare professionals are asked to sign up via the website or to call the assessment team if they are interested in participating. When a healthcare professional indicates continued interest in participating in the study during the call, an information letter and consent form for healthcare professionals will be sent out by mail and the healthcare professional can then sign the informed consent form.

### Outcome measures

#### Overview

We will compare the utility of PRIME Parkinson care to usual care on five dimensions, each of which covers a single primary endpoint and several secondary endpoints. The single overall primary endpoint of this study is an endpoint that reflects the health dimension: parkinsonism-related complications. Since we anticipate that stand-alone analyses for other dimensions will be conducted, we have also defined a primary endpoint for each dimension, which is presented in the next paragraphs. An overview of all outcome measures and covariates is provided in Table 4.

**Table 4 Tab4:** Overview of outcome measures in questionnaire-based assessments

*Persons with parkinsonism*		
**Dimension**	**Outcome**	**Instrument**
Health	Quality of life	Parkinson’s Disease Questionnaire-39 (PDQ-39) [26]
	Depressive symptoms	Beck Depression Inventory II [27]
	Anxiety	State Trait Anxiety Inventory for Adults [28]
	Autonomic symptoms	Scales for Outcomes in Parkinson’s Disease—Autonomic Dysfunction (SCOPA-AUT)[29]
	Cardinal motor features	Numeric rating scale for bradykinesia, tremor, rigidity, postural imbalance and Movement Disorders Society Unified Parkinson Disease Rating Scale (MDS-UPDRS) part II on motor functions in daily life [30]
	Freezing	New Freezing of Gait Questionnaire [31]
	Acceptance of Illness	Acceptance of Illness Scale [32]
	Coping strategy	Ways of Coping Questionnaire [33]
	Activities of Daily Living	Self-assessment Parkinson’s Disease Disability score [34]
	Cognitive performance	Telephone Montreal Cognitive Assessment (MoCA) [35]
Patient experience	Integrated Care	Patient Assessment of Chronic Illness Care + (PACIC +) [36]
	Continuity of care	Nijmegen Continuity of care questionnaire [37]
	Self-management	Patient Activation Measurement (PAM) [38]
*Carers*		
Carer experience	Carer burden	Zarit Carer Burden Inventory [39]
	Self-management	Patient-activation measure – Caregivers (PAM-CG) [40]
	Quality of life of Carer	Parkinson’s Disease Questionnaire-Carers [41]
	Coping strategy of Carer	Brief COPE (Coping Orientation to Problems Experienced) [42]
	Social support of Carer	Multidimensional Scale of Perceived social support [43]
*Healthcare Professionals*		
Healthcare professional experience	Healthcare Professional wellbeing	Professional Fulfilment Index [44]
	Integrated Care	Assessment of chronic illness care (ACIC) [45]
	Shared decision making	The 9-item Shared Decision Making Questionnaire (SDM-Q-9) [46]

#### Primary dimension: health

The primary endpoint of the health dimension is the number of parkinsonism-related complications. A parkinsonism-related complication is defined as one of the following events: sustaining a fracture or other orthopaedic injury, urinary tract infection, pneumonia, neuro-psychiatric disorders (delirium, psychosis, hallucinations, mood disorders and anxiety). To determine the occurrence of these events we will use the following proxies in the nationwide healthcare claims-based database from Vektis: having a new (unscheduled) hospital visit or crisis (non-elective) admission, a new drug prescription (for example ATC N06AA codes in the case of a depression) or another type of new care intervention related to a parkinsonism-related complication [47, 48]. Previous studies show a very high specificity but lower sensitivity for the use of Anatomical Therapeutic Chemical (ATC) codes to identity complications, for example a sensitivity of 44–54% and specificity of 89–93% for depression [49]. To raise the sensitivity, we combine Diagnosis-related group (DRG) codes and ATC codes from medical claims data. Several studies show the application of usage of medical claims data in Parkinson's disease research and use DRG and ATC drug prescription claims information as proxies for complications or disease severity [50–52]. For example, the use of ATC N05A and N06D as an indicator for respectively antipsychotics and anti-dementia drugs (which covers both anticholinesterases and other anti-dementia drugs) [52].We have previously used a similar composite endpoint in a healthcare claims-based data study on specialized physiotherapy [53], although we note that the composite endpoint in that study only comprised mobility-related complications and pneumonia. Given the wide scope of targeted preventable complications in PRIME Parkinson care, we have now broadened the definition of that composite endpoint. In secondary analyses on the health dimension which are based on questionnaire-based data, the primary endpoint will be quality of life measured using Parkinson’s Disease Questionnaire-39 (PDQ-39).

#### Secondary dimensions

The primary endpoint of the cost of healthcare dimension is total cost of care, which entails community care, hospital care and pharmaceutical expenditure. Secondary endpoints within this dimension include the distribution of costs over community or hospital care and, separately, costs of parkinsonism-related complications. This approach is similar to our approach in a previously published study [53]. For patient experience the primary endpoint will be Patient Assessment of Chronic Illness Care + (PACIC +)[36]. To evaluate carer experience, the primary endpoint will be Zarit Carer Burden Inventory [39]. The Professional Fulfilment Index [44] will be the primary endpoint for healthcare professional experience. To measure the fidelity and implementation of the elements of the new model of care, which replaces the usual care, the Nijmegen Continuity of care questionnaire will be used as measure for the continuity of care, and the PACIC + which looks at integrated care, and which is a part of Personalized care [36, 37]. Next to the questionnaire data, several process indicators will be used to assess the fidelity of the new model of care: more in-depth data on the usage of the regional PRIME Parkinson helpdesk for persons with Parkinsonism and carers, usage of information databank by professionals, carers and persons with Parkinson and the usage of the Parkinson nurse.

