We believe that empirical insight on the potential utility of PRIME Parkinson care may be generalisable to other disorders, as parkinsonism can be regarded as a “model condition” for many other chronic neurological disorders, given its wide-ranging clinical phenotype, involvement of multiple professional disciplines in care, multimodal management (e.g., pharmacotherapy, neurosurgical procedures), the long disease duration, and relatively high prevalence [12]. Furthermore, we hypothesize that due to the proactive and collaborative nature of PRIME Parkinson care, persons will be empowered to function better with parkinsonism, leading to improvements in health and patient experience of care -as well as beneficially affecting carer experience and healthcare professional wellbeing- while maintaining cost neutrality. Should this hypothesis be confirmed, then a financial model for this novel care package will have to be developed to demonstrate sustainability and facilitate possible dissemination and implementation to other regions and other high income countries.

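### The cost endpoint counts insurance claims only, so any PRIME delivery cost not billed to insurers is left out and the comparison tilts in PRIME's favour

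*Protocol article*

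**What the plan says.** Under Outcome measures, Secondary dimensions, the protocol article makes the primary cost endpoint "total cost of care, which entails community care, hospital care and pharmaceutical expenditure". No component covers the cost of running the programme.

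The source is given three times and is always the same. The abstract's Methods paragraph says "We will use healthcare claims-based data to evaluate the primary endpoint, and costs of healthcare". The text before Table 2 uses claims for the primary endpoint "as well as other endpoints of health and cost of healthcare". Table 2 lists healthcare claims alone against cost, although it lists two sources against health. The claims come from a national centre that "has healthcare expenditure data on all insured individuals in The Netherlands".

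The same Secondary dimensions paragraph states that "several process indicators will be used to assess the fidelity of the new model of care". These include "usage of the regional PRIME Parkinson helpdesk for persons with Parkinsonism and carers", use of an information databank and use of the Parkinson nurse. All are measured as usage; no cost is attached to any of them.

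Two further statements bear on financing. In the design overview: "The choice to include four community hospitals in the PRIME Parkinson care region was determined by the available funding". In the Discussion, should the study's hypothesis be confirmed, "a financial model for this novel care package will have to be developed to demonstrate sustainability". The Background gives cost neutrality as an aim of the care model, and the Discussion gives it as part of the hypothesis.

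**The concern.** A claims database sees the cost of a care model only where that cost is billed for an insured person. A regional helpdesk or a shared databank is not obviously billed that way. If part of PRIME is paid by another route, the index region's measured total leaves out part of the intervention being evaluated.

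The error would run one way. PRIME would look cheaper than it is on the endpoint that the article names as primary for its cost dimension, and for which it foresees stand-alone analyses. A finding of neutrality or savings would then feed into the financial model and any spread to other regions.

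**Working it through.** The article gives no cost figure, so there is no stated result to reproduce. The check has two parts: whether the design would remove an omitted cost, and how the amount scales.

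**Inputs**
- Cost endpoint and single source: Secondary dimensions; abstract; Table 2.
- Contrast: difference-in-difference between regions over time, which the Discussion intends for the claims-based outcomes.
- Additional cost covariate: total cost of care in years before the study (Covariates).
- Index region: an estimated 2,000 persons (abstract).
- Annual unbilled spending: not given. Assumed range, for illustration only, 100,000 to 1,000,000 euro.

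**Step 1: does the contrast remove the omission?** Write full mean cost per person-year as claims cost plus unbilled cost U, for region (P = PRIME, C = usual care) and period (0 = before, 1 = after). Then

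claims difference-in-difference = full difference-in-difference − X, where X = (U_P1 − U_P0) − (U_C1 − U_C0).

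Unbilled overhead that is stable over time cancels within its own region. A PRIME element that starts with implementation enters U_P1 only, so it stays in X in full. It coincides with the region-by-period interaction that the analysis estimates. Adjustment for pre-study cost does not help, because that covariate predates the element. The −X identity is exact for differences in mean cost; a model on a ratio scale would be shifted in the same direction, by an amount that depends on mean cost.

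**Step 2: size of X.** X = annual unbilled spending / index persons.

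| Assumed unbilled spending per year (euro) | Calculation | X per person-year (euro) |
|---|---|---|
| 100,000 | 100,000 / 2,000 | 50 |
| 250,000 | 250,000 / 2,000 | 125 |
| 500,000 | 500,000 / 2,000 | 250 |
| 1,000,000 | 1,000,000 / 2,000 | 500 |

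**Step 3: what claims would show.**

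| True difference (euro) | X (euro) | Claims difference (euro) | Reading |
|---|---|---|---|
| +500 | 125 | 500 − 125 = +375 | excess shrunk |
| +250 | 250 | 250 − 250 = 0 | excess hidden, apparent neutrality |
| +250 | 500 | 250 − 500 = −250 | excess shown as a saving |
| 0 | 250 | 0 − 250 = −250 | neutrality shown as a saving |
| −250 | 250 | −250 − 250 = −500 | saving exaggerated |

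For any X above zero the shift favours PRIME. It moves the estimate closer to zero only if PRIME truly costs more and X is less than twice that excess.

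**The case against.** The strongest reply is that no unbilled cost has been shown to exist. A reader might infer from the two financing statements that part of PRIME, including staff, is paid from project money. The article does not say so. It does not state what the available funding pays for. The financial model is conditional on success and looks ahead to sustainability and spread. The article also presents PRIME as a replacement of usual care and not as a research intervention, and Parkinson nurse contacts may well be billed. This stands: the omission is possible, not demonstrated. Only the helpdesk is labelled as PRIME's own; the article does not say whether the databank is new or confined to the region.

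A reader might also infer that the usual-care total is complete. Nothing supports that either, since usual care may carry unbilled organisational cost. Step 1 shows that such cost matters only if it changes between periods.

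It can also be said that claimed expenditure is a recognisable payer perspective, that an economic evaluation is announced, and that secondary analyses are deferred to a separate plan. A payer perspective is legitimate if the conclusion is confined to it, but neutrality is hypothesised without that limit. The economic evaluation names no other cost source. The deferral covers the analysis approach and sample sizes, whereas the endpoint's components and source are already fixed in the article. These replies do not remove the point.

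**Conclusion.** The concern holds as a risk built into a stated choice of endpoint and source. If PRIME has delivery cost X per index person-year that is not billed to insurers and begins with implementation, the claims-based comparison understates PRIME's cost by X, and neither the difference-in-difference nor adjustment for earlier cost corrects it. The scale is 50 euro per person-year for each 100,000 euro per year unbilled. This assumes 2,000 index persons and no change in unbilled usual-care cost.

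The true X is unknown and could be zero. Two stronger readings are not supported. One is that the bias always runs toward neutrality: if PRIME is truly neutral, the error is a false saving. The other is that a particular percentage excess would be reported as neutral: the article gives neither the unbilled spending nor the mean claims cost from which to work one out.

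The matter is confined to a secondary dimension. The overall primary endpoint, parkinsonism-related complications, is not affected.

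**What to change.** - State the costing perspective and, for the helpdesk, databank and any additional nurse or coordination time, whether the cost is billed to insurers. If all of it is billed, one sentence saying so closes the point.
- Otherwise, record the recurring delivery cost of the unbilled elements. Exclude research expense, one-off start-up expense and anything already in claims.
- Divide that cost by index person-years and add it to the index side after implementation. Treat comparable unbilled usual-care overhead in the same way where it is known.
- Base the cost-neutrality conclusion on this total and report claims-only cost separately as an insurer-perspective result.
- If delivery cost is not added, limit the conclusion to insurer-reimbursed cost.

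The price is a short addition to the endpoint definition and an extract from the project accounts. No new data are needed from participants, and usage of the three elements is already to be collected. The cost result may become somewhat less favourable to PRIME.
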